## **8.8. Regulatory reporting requirements for serious adverse events**

The investigator will promptly report all SAEs to GSK in accordance with the procedures detailed in Section 8.7. GSK Biologicals has a legal responsibility to promptly notify, as appropriate, both the local regulatory authority and other regulatory agencies about the safety of a product under clinical investigation. Prompt notification of SAEs by the investigator to the Study Contact for Reporting SAEs is essential so that legal obligations and ethical responsibilities towards the safety of other subjects are met.

The investigator, or responsible person according to local requirements, will comply with the applicable local regulatory requirements related to the reporting of SAEs to the IRB/IEC and, if required, to the applicable government authority.

Investigator safety reports are prepared according to the current GSK policy and are forwarded to investigators as necessary. An investigator safety report is prepared for a SAE(s) that is both attributable to investigational product and unexpected. The purpose of the report is to fulfill specific regulatory and Good Clinical Practice (GCP) requirements, regarding the product under investigation.

An investigator who receives an investigator safety report describing a SAE(s) or other specific safety information (e.g., summary or listing of SAEs) from GSK Biologicals will file it with the Investigator Brochure or other appropriate study documentation and will notify the IRB or IEC, if appropriate according to local requirements.

## **8.9. Post-study adverse events and serious adverse events**

A post-study AE/SAE is defined as any event that occurs outside of the AE/SAE detection period defined in Section 8.4. Investigators are not obligated to actively seek AEs or SAEs in former study participants.

However, if the investigator learns of any SAE, including a death, at any time after a subject has been discharged from the study, and he/she considers the event reasonably related to the investigational product, the investigator will promptly notify the Study Contact for Reporting SAEs.

## **8.10. Pregnancy**

Not applicable.

## **8.11. Treatment of adverse events**

Treatment of any adverse event is at the sole discretion of the investigator and according to current good medical practice. Any medication administered for the treatment of an AE should be recorded in the subject's CRF. Refer to Section 6.9.

## **9. SUBJECT COMPLETION AND WITHDRAWAL**

### **9.1. Subject completion**

A subject who returns for the concluding visit/is available for the concluding contact foreseen in the protocol is considered to have completed the study.

A subject that comes for Clinic Visit 6 has completed the primary study phase. A subject that comes for Clinic Visit 7 has completed the extended follow-up phase of the study.

### **9.2. Subject withdrawal**

Subjects who are withdrawn because of AEs must be clearly distinguished from subjects who are withdrawn for other reasons. Investigators will follow subjects who are withdrawn as result of a SAE/AE until resolution of the event (see Section 8.6). Withdrawals will not be replaced.

#### **9.2.1. Subject withdrawal from the study**

From an analysis perspective, a 'withdrawal' from the study is any subject who was not available for the concluding contact foreseen in the protocol. A subject that comes for Clinic Visit 6 has completed the primary study phase. A subject that comes for Clinic Visit 7 has completed the extended follow-up phase of the study.

A subject qualifies as a 'withdrawal' from the study when no study procedure has occurred, no follow-up has been performed and no further information has been collected for this subject from the date of withdrawal/last contact.

Investigators will make an attempt to contact those subjects who do not return for scheduled visits or follow-up.

Information relative to the withdrawal will be documented on the Study Conclusion page of the CRF. The investigator will document whether the decision to withdraw from the study was made by the subject's parent or guardian or the investigator and which of the following possible reasons was responsible for withdrawal:

- serious adverse event.
- non-serious adverse event.
- protocol violation (specify).
- consent withdrawal, not due to an adverse event.
- moved from the study area.
- lost to follow-up.
- death.
- other (specify).

**9.2.2. Subject withdrawal from investigational product**

A 'withdrawal' from the investigational product is any subject who does not receive the complete treatment, i.e. when no further planned dose is administered from the date of withdrawal. A subject withdrawn from the investigational product may not necessarily be withdrawn from the study as further study procedures or follow-up may be performed (safety or immunogenicity) if planned in the study protocol.

Information relative to premature discontinuation of the investigational product will be documented on the Vaccine Administration page of the CRF. The investigator will document whether the decision to discontinue further vaccination/treatment was made by the subject's parent or guardian or the investigator and which of the following possible reasons was responsible for withdrawal:

- serious adverse event.
- non-serious adverse event.
- other (specify).

**10. DATA EVALUATION: CRITERIA FOR EVALUATION OF OBJECTIVES****10.1. Primary endpoint**

**NOTE:** *In the event that malaria rates are lower in the year of the study the cross sectional survey, unblinding and analysis scheduled at 4½ months post Dose 3 will be delayed until approximately 245 children have experienced an episode.*

- Time to first case of malaria meeting the primary case definition over a period starting 14 days after Dose 3 and extending for 4 months.

**10.2. Secondary endpoints****Efficacy**

- Time to first case of malaria meeting the secondary case definition over a period starting 14 days after Dose 3 and extending for 4 months.
- Multiple events of malaria meeting the primary case definition over a period starting 14 days after Dose 3 and extending for 4 months.
- Multiple events of malaria meeting the secondary case definition over a period starting 14 days after Dose 3 and extending for 4 months.
- Parasite prevalence and density at 4½ months post Dose 3.
- Hemoglobin at 4½ months post Dose 3.

**Safety**

- Occurrence of solicited symptoms and local reactions over a 7-day follow-up

period (day of vaccination and 6 subsequent days) after each vaccination.

- Occurrence of unsolicited symptoms over a 30-day follow-up period (day of vaccination and 29 subsequent days) after each vaccination.
- Occurrence of serious adverse events from the time of first vaccination (Month 0) until 4½ months post Dose 3 (Month 6½).
- Occurrence of parameters of hematological monitoring outside acceptable ranges.

#### **Immunogenicity**

- Anti-CS antibody titers prior to vaccination, 1 month post Dose 3 and 4½ months post Dose 3.
- Anti-HBs antibody titers prior to vaccination and 1 month post Dose 3.
- Frequency of CD4+ and CD8+ CS-specific T-cells expressing at least two of the following: IL-2, CD40L, TNF- $\alpha$  and IFN- $\gamma$  prior to vaccination and 1 month post Dose 3.

### **10.3. Tertiary endpoints**

#### **Efficacy**

- Time to first case of malaria meeting the primary case definition over a period starting 14 days after Dose 3 and extending for 12 months *and a period starting 14 days after Dose 3 and extending until October 2008 in Kilifi and September 2008 in Korogwe.*

*Amended 17 April 2008*

- Time to first case of malaria meeting the secondary case definition over a period starting 14 days after Dose 3 and extending for 12 months *and a period starting 14 days after Dose 3 and extending until October 2008 in Kilifi and September 2008 in Korogwe.*

*Amended 17 April 2008*

- Multiple events of malaria meeting the primary case definition over a period starting 14 days after Dose 3 and extending for 12 months *and a period starting 14 days after Dose 3 and extending until October 2008 in Kilifi and September 2008 in Korogwe.*

*Amended 17 April 2008*

- Multiple events of malaria meeting the secondary case definition over a period starting 14 days after Dose 3 and extending for 12 months *and a period starting 14 days after Dose 3 and extending until October 2008 in Kilifi and September 2008 in Korogwe.*

*Amended 17 April 2008*

- Parasite prevalence and density at 12 months post Dose 3 *and in October 2008 in Kilifi and in September 2008 in Korogwe.*

*Amended 17 April 2008*

- Hemoglobin at 12 months post Dose 3 *and in October 2008 in Kilifi and in September 2008 in Korogwe.*

*Amended 17 April 2008*

#### **Safety**

- Occurrence of SAEs throughout the entire study period.

#### **Immunogenicity**

- Anti-CS antibody titers at 12 months post Dose 3 (Month 14) *and in October 2008 in Kilifi and in September 2008 in Korogwe.*

*Amended 17 April 2008*

- Anti-HBs antibody titers at 12 months post Dose 3.
- Frequency of CD4+ and CD8+ CS-specific T-cells expressing at least two of the following: IL-2, CD40L, TNF- $\alpha$  and IFN- $\gamma$  prior to vaccination and 12 months post Dose 3.

### **10.4. Exploratory endpoint**

#### **Immunogenicity**

- Numbers of IFN- $\gamma$  producing cells upon CS stimulation in short and long term culture Elispot assays at baseline, one month and 12 months post Dose 3.
- Frequency of malaria antigen-specific effector cells and regulatory T-cells and levels of expression of effector and regulatory cytokines at 4½ months post Dose 3.
- Anti-malaria blood stage antigens antibody levels at baseline, one month, 4½ months and 12 months post Dose 3.

### **10.5. Case Definitions for Malaria**

**Primary malaria case definition** *P falciparum* infection > 2 500 parasites per  $\mu$ L in a child with a documented fever  $\geq 37.5^{\circ}\text{C}$  (axillary) detected by ACD or PCD.

**Secondary malaria case definition** *P falciparum* infection > 0 parasites per  $\mu$ L in a child with a documented fever  $\geq 37.5^{\circ}\text{C}$  (axillary) detected by ACD or PCD.

Amended 23 October 2006

## **10.6. Estimated sample size**

### **10.6.1. Power Calculations**

The final analysis is projected to occur after the completion of 4 months of surveillance, at which time it is assumed that 36% of children in the control group will have been affected by a malaria episode. Assuming a true vaccine efficacy of 30% and an attack rate of 36% in controls (corresponding to an attack rate of 25.2% in vaccinees), a sample size of 400 evaluable subjects per group has 90% power to detect a difference between groups using a 2-sided Fisher exact test at 5% significance level. The final analysis is projected to occur after the completion of 4 months of surveillance, at which time it is assumed that 36% of children in the control group will have been affected by a malaria episode. However, in the event that malaria rates are lower in the year of the study, the unblinding and analysis will be delayed until approximately 245 children have experienced an episode ( $400 \times 36\% + 400 \times 25.2\% = 245$ ). This analysis will also have 90% power.

The assumption of 36% attack rate in controls is based on epidemiological data collected at the two sites. In Kilifi the proportion of children aged 12 to 18 months olds affected by a malaria episode using the same ACD methodology as proposed in this document over the same time frame in 2005 was 37% (personal communication [name]). In Korogwe the case rate was 34% determined in children aged 5 to 17 months in Mkokola village (10 km from Korogwe) by Passive Case Detection at village level (personal communication [name], [name]).

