Subsequently, a large safety, immunogenicity and efficacy trial in children aged 1 to 4 years from an area of high transmission was conducted in Mozambique, enrolling a total of 2022 subjects (Malaria-026 [Report, GSK data on file]; [Alonso 2004]; [Alonso 2005]). In this study, 3 doses of RTS,S/AS02A (0.25 mL dose) were administered according to a 0, 1, 2-month schedule to approximately 1000 children. The primary endpoint of this trial investigated vaccine efficacy against the onset of clinical malaria disease. Up to six months post Dose 3, the VE determined as the time to the first clinical episode (after adjustment for covariates) was 29.9% (95% CI: 11.0 to 44.8;  $p = 0.004$ ). For the entire study period, up to 18 months post Dose 3, VE for the same endpoint was 32.8% (95% CI: 20.1 to 43.4;  $p = 0.0001$ ).

The trial also offered the opportunity to investigate VE against multiple attacks of malaria and severe malaria. Against multiple attacks, VE was 27.4% (95% CI: 6.2 to 43.8;  $p = 0.014$ ) up to six months post Dose 3. For the entire study period, VE was 32.4% (95% CI: 17.6 to 44.5;  $p = 0.0001$ ). Against severe malaria, VE was 57.7% (95% CI: 16.2 to 80.6;  $p = 0.019$ ) over six months post Dose 3: for the entire study period VE was 48.6% (95% CI 12.3 to 71.0;  $p = 0.02$ ).

During the single-blind phase (Months 8½ to 21) in both Cohort 1 and 2, the proportion of children experiencing a SAE was similar in the RTS,S/AS02A and control groups

(5.1% vs. 6.8%, respectively). However, in the overall surveillance period (Months 0 to 21), there was a tendency for the proportion of children experiencing a SAE to be lower in the RTS,S/AS02A group compared to the control groups in both Cohorts 1 and 2 (20.9% vs. 28.6%, respectively). The pattern of morbidity was similar to that previously observed at the study site and described in the region. At least 97% of recipients of RTS,S/AS02A were seropositive for anti-CS antibodies and at least 97% of recipients of RTS,S/AS02A were seroprotected for anti-HBs antibodies 18 months post Dose 3 [Alonso, 2005].

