### **10.9. Statistical methods for Vaccine Efficacy endpoints**

#### **10.9.1. Time to event analyses**

For time to endpoints (time to first or only episode of *P. falciparum* malaria), the incidence of episodes (episodes/person years at risk) for each group will be presented. Kaplan-Meier curves for both groups will be shown. The distribution of the “time to” will be compared with the Wilcoxon test (if efficacy varies with time) or the Log-rank test (if it does not). Vaccine Efficacy will be assessed using Cox regression models. Vaccine

efficacy is defined as 1 *minus* R where R is the hazard ratio of the RTS,S/AS01E group versus the Control group (with 95% CI). Crude and adjusted estimates for covariates (possible covariates include: study center, bed-net use, geographical area and distance from health center) will be presented.

Cox regression assumes proportional hazards throughout the follow-up period. This assumption will be checked by plotting per group the log of the cumulative hazard against the log of time. Under the assumption of proportionality of the hazard, both curves should be parallel. A test based on the Schoenfeld residuals will be performed.

If there is strong evidence that the hazard is not constant over the surveillance period, then alternative approaches to analyze the data may be examined according to the following:

- Cox regression models with time varying covariates, using fractional polynomials to identify the function of the time that best fits. The following functions of the time will be explored : -2, -1, -1/2, log, identity, 1/2, 2, 3. The Akaike's criterion and the Schwarz Bayesian criterion will be explored.
- Accelerated failure time (AFT) models using 'Generalized Gamma', 'Standard Gamma', 'log-normal', 'weibull' and 'exponential' distributions.

In order to assess the goodness-of-fit of these models, a graphical representation of the expected survival curve against the observed using the Kaplan-Meier methodology will be presented. Where appropriate, likelihood ratio tests will be carried out to investigate the goodness-of-fit of the different models if appropriate.

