## **10.10. Final analyses**

The final analysis will be conducted on data collected until Clinic Visit 6. The study will continue in a single-blind manner. This additional information will be appended to the study report.

In the event that malaria rates are lower in the year of the study the unblinding and analysis following Clinic Visit 6 will be delayed until approximately 245 children have experienced an episode. This analysis will have 90% power assuming true vaccine efficacy to be 30%.

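### The 90% power holds for 30% efficacy as 1 minus a risk ratio; for 30% efficacy as the protocol defines it, 1 minus the hazard ratio, power is about 80%

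*Protocol*

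**What the plan says.** Section 10.6.1 starts from this scenario after four months of surveillance: "Assuming a true vaccine efficacy of 30% and an attack rate of 36% in controls (corresponding to an attack rate of 25.2% in vaccinees". For that contrast it claims that "a sample size of 400 evaluable subjects per group has 90% power to detect a difference between groups"; the calculation is for Fisher's exact test, two-sided at the 5% level. If malaria rates are low, unblinding and analysis are "delayed until approximately 245 children have experienced an episode", where 245 is 400 × 36% + 400 × 25.2%. It then adds: "This analysis will also have 90% power".

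Section 10.10 repeats the claim for the delayed analysis without the attack rates: "This analysis will have 90% power assuming true vaccine efficacy to be 30" per cent. The synopsis and Section 3 give the 30% efficacy, the 36% control rate and the 90% power, but not the 25.2%.

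The primary endpoint (Section 10.1) is time to first case meeting the primary case definition, from 14 days after Dose 3 for four months. Section 10.9.1 assesses efficacy by Cox regression and defines it as 1 minus R, "where R is the hazard ratio of the RTS,S/AS01E group versus the Control group".

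**The concern.** The same words, 30% vaccine efficacy, describe two different effects. In the power section the vaccinee attack rate is obtained by multiplying the control rate by 0.70, so efficacy is 1 minus the risk ratio. In the analysis section it is 1 minus the hazard ratio. For rare events the two nearly coincide; at a 36% attack rate they do not.

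A reader who takes 30% in the only sense that Section 10.9.1 defines for the primary endpoint will conclude from Section 10.10 that such an effect would be missed one time in ten. On that scale it would be missed about one time in five. The claim is attached to the 245-child rule for breaking the blind, where power in a log-rank or Cox analysis depends mainly on the event count and the hazard ratio. The mismatch therefore affects a stated design property at the point where it is used.

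**Working it through.** **Inputs**, all from the protocol: control attack rate 36%, vaccinee attack rate 25.2%, 400 evaluable per group, two-sided 5%, 245-child trigger (Section 10.6.1); 1:1 allocation (Section 3); efficacy as 1 minus the hazard ratio (Section 10.9.1); about 445 enrolled per group (synopsis).

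**1. Reproduce the stated figure.** Full enumeration of the two-sided Fisher exact test, 0.36 versus 0.252 with 400 per group, gives power 90.2%. Events: 400 × 0.36 + 400 × 0.252 = 244.8, or 245. Both stated figures reproduce.

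**2. Put the planned contrast on the analysis scale.** Under proportional hazards and complete follow-up, 1 − p_vaccine = (1 − p_control)^HR, so

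HR = ln(1 − 0.252) / ln(1 − 0.36) = ln 0.748 / ln 0.64 = 0.651.

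This is an efficacy of 34.9% as Section 10.9.1 defines it.

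**3. Power for that contrast at 245 events.** The Schoenfeld formula is power = Φ(√D/2 × |ln HR| − 1.960). With √245/2 = 7.826 and |ln 0.651| = 0.430, the argument is 3.364 − 1.960 = 1.404 and power is 92.0%. The Freedman formula gives 91.2%. A simulated log-rank test with 400 per group (20,000 runs, exponential times) gives 91.4%.

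**4. Power for 30% efficacy as defined (HR 0.70) at 245 events.** |ln 0.70| = 0.357; 7.826 × 0.357 = 2.791; 2.791 − 1.960 = 0.831; power is 79.7%. The Freedman formula gives 78.9%.

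**5. Power for HR 0.70 with 400 per group over four months.** Vaccinee attack rate = 1 − 0.64^0.70 = 26.8%. Events = 400 × (0.36 + 0.2683) = 251.

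| Method | Power |
|---|---|
| Schoenfeld | 80.7% |
| Simulated log-rank | 80.6% |
| Freedman | 79.9% |
| Fisher exact | 77.8% |

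**6. If all 445 per group contribute.** Events = 445 × 0.6283 = 280; Schoenfeld power is 84.7%.

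**7. Efficacy with 90% power at 245 events.** 1 − exp(−2 × 3.2415/√245) = 1 − exp(−0.414) = 33.9%, where 3.2415 = 1.960 + 1.282.

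**The case against.** The best defence is that Section 10.6.1 discloses its whole scenario: both attack rates, the test, the level and the group size. Under those conditions its figures are right. Moving from Fisher to a log-rank or Cox analysis does not lose power for that contrast; it gains slightly (about 92% against 90.2%). The 80% appears only when the printed 25.2% is replaced by 26.8%. All of this stands, and it makes the fault a mismatch of scales. A reader might infer an arithmetic error, or that the planned contrast is underpowered; neither is so. The defence does not cover Section 10.10, the synopsis or Section 3, where 30% appears without the vaccinee attack rate, while the protocol's definition of efficacy for this endpoint is on the hazard scale.

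The conversion also needs proportional hazards, and Section 10.9.1 makes provision for their failure. If they fail, attack rates do not map to a single hazard ratio. The 80% is therefore conditional, and the fix says so. The Total Cohort is analysed as well, which is why the range extends to about 85%.

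Two further inferences are tempting and not supported:

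- *That the 30% was taken from the earlier trial in Mozambican children and so belongs on the hazard scale.* Section 1.4 reports of that trial that "the VE determined as the time to the first clinical episode (after adjustment for covariates) was 29.9" per cent. The protocol does not say that the planning value came from there. That estimate is covariate-adjusted and covers six months, and the passage names neither a hazard ratio nor a Cox model.
- *That the trigger should be raised.* By the Schoenfeld formula, 90% power at HR 0.70 needs 331 first episodes. The existing delay rule applies only when rates are lower than expected. At the expected 36%, HR 0.70 yields 251 episodes, and 331 among 800 children would need about 47% of controls affected. Unblinding would then be delayed beyond the four-month window even if rates were as planned. That would be a new design choice.

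**Conclusion.** The point holds as an inconsistency of scale, and the Section 10.10 sentence is wrong as written when efficacy has the meaning given in Section 10.9.1. The planned numbers give about 90% power for 36% versus 25.2%, which is about 35% efficacy as 1 minus the hazard ratio. For 30% on that scale power is about 80% at 245 events: 77.8% to 80.7% across methods with 400 per group, and at most about 85% with all 445. The chance of missing such an effect is thus about 20%, or about 15% in the most favourable case, against the stated 10%.

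This rests on proportional hazards, a 36% control attack rate and complete four-month follow-up; the figures at the 245-event trigger depend on the event count rather than on the last two. The efficacy estimate, its confidence interval and the type I error are not affected.

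**What to change.** In the synopsis and Sections 3, 10.6.1 and 10.10, state both scales, for example: *The 90% power refers to attack rates of 36% versus 25.2% (risk ratio 0.70; about 35% efficacy as 1 minus the hazard ratio). Assuming proportional hazards, about 245 first episodes give about 80% power for 30% efficacy as defined in Section 10.9.1 (hazard ratio 0.70) and 90% power for an efficacy of about 34%.*

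Correct the Section 10.10 sentence on power at 30% efficacy accordingly, and qualify the closing power sentence on the delayed analysis in Section 10.6.1 in the same way.

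The cost is protocol wording and a less favourable power statement. Endpoint, model, tests, enrolment and the 245-child trigger are unchanged. By the date of Amendment 4 (April 2008) vaccination had begun and post-Dose-3 surveillance was under way (Section 1.6.4), so the restatement describes the design accurately and does not alter the sample size.
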